## Abstract

**Background:**

Progressive Supranuclear Palsy (PSP) is a sporadic and progressive neurodegenerative disease which belongs to the family of tauopathies and involves both cortical and subcortical structures. No effective therapy is to date available.

**Methods/design:**

Autologous bone marrow (BM) mesenchymal stem cells (MSC) from patients affected by different type of parkinsonisms have shown their ability to improve the dopaminergic function in preclinical and clinical models. It is also possible to isolate and expand MSC from the BM of PSP patients with the same proliferation rate and immuphenotypic profile as MSC from healthy donors. BM MSC can be efficiently delivered to the affected brain regions of PSP patients where they can exert their beneficial effects through different mechanisms including the secretion of neurotrophic factors.

Here we propose a randomized, placebo-controlled, double-blind phase I clinical trial in patients affected by PSP with MSC delivered via intra-arterial injection.

**Discussion:**

To our knowledge, this is the first clinical trial to be applied in a no-option parkinsonism that aims to test the safety and to exploit the properties of autologous mesenchymal stem cells in reducing disease progression. The study has been designed to test the safety of this “first-in-man” approach and to preliminarily explore its efficacy by excluding the placebo effect.

**Trial registration:**

NCT01824121

## Background

Progressive supranuclear palsy (PSP) is a rare form of parkinsonism with a prevalence of about 0.5 cases per 100,000 inhabitants and with an incidence of 5.3 new cases every 100,000 inhabitants [1,2]. Its etiology is unknown. From a pathological point of view, the disease consists in a neurodegenerative process that involves the basal ganglia, the brainstem, the prefrontal cortex and the cerebellum, with accumulation of a tau protein - hence the classification as tauopathy [3]. Onset typically occurs after 40 years of age. The symptoms include bradykinesia, proximal and axial rigidity and early postural instability. The key sign, which gives the disease its name, is the supranuclear paralysis of vertical gaze, followed by abnormalities of horizontal gaze. This sign usually appears three or four years after the onset of motor symptoms. The most disabling symptoms, especially in the early phases of the disease, are stiff, upright posture and abnormal gait with a very broad base associated with severe postural instability and frequent falls, especially backwards. The patient is confined to a wheelchair on average after 5 years of disease. Levodopa response is poor or absent [4-6]. Mean survival amounts to 7 years [7]. Early falls, speech and swallowing problems, diplopia and early insertion of a percutaneous gastrostomy are predictors of reduced survival [8].

The differential diagnosis between PSP and the other parkinsonisms is made according to clinical criteria [9]. Molecular biology studies have shown that the parkinsonisms share a common pathogenesis, namely the intraneuronal accumulation of misfolded proteins that cannot be removed normally. The misfolding is caused by structural abnormalities due to genetic mutation and/or exposure to environmental factors [10]. The syndromes have been classified according to the kind of misfolded proteins that accumulate: synucleinopathies, in which the main accumulated protein is alpha-synuclein, and tauopathies, in which it is protein tau [11]. Unfortunately the greater understanding of the parkinsonisms in terms of molecular biology has not resulted in the finding of a cure. At present all these movement disorders are incurable. However, symptomatic treatment is available. It consists mainly in dopaminergic treatment (levodopa and dopamine agonists), which controls symptoms for several years in Parkinson’s Disease (PD), whereas the response is generally poor and short-lived in the other syndromes [12]. Moreover, even in PD it is not effective on the most disabling symptoms, such as postural instability and freezing. Also surgical treatment is available. It consists in the implantation in strategic positions of electrodes for deep brain stimulation, which corrects electrical circuit imbalances occurring in circumscribed parts of the brain in PD patients [13,14]. However, this treatment is not suitable for the other syndromes, in which the neurodegenerative process is more extensive and general conditions deteriorate more rapidly.

### Summary of pre-clinical data to support the use of autologous MSC in PSP patients

Mesenchymal stem cells (MSC) are multipotent cells that can be isolated from many sources, including bone marrow (BM). Besides their in vitro and in vivo potential to transdifferentiate into several mesodermal lineages, their therapeutic relevance is mostly due to their immunosuppressive and anti-inflammatory properties [15]. Other paracrine actions of MSC have been claimed to act in several animal models of diseases and also in preliminary clinical trials [16-18]. Indeed, the real MSC trans-differentiation capacity seems to have limited clinical relevance, with the exception of bone differentiation that is currently exploited in different orthopaedic trials [19]. The main expected pharmacological effect of BM MSC on dopaminergic neurons that support their use in PSP is the potential to regulate cell differentiation and function by reducing oxidative stress and apoptosis. Regarding this potential mechanism of action, there are several experimental evidences of the neurotrophic effect of MSC that result in the reduction of tissue damage and neuronal loss. The brain derived neurotrophic factor (BDNF) and the glial derived neurotrophic factor (GDNF) have been recently identified as the putative mediators of this effect. BDNF is a protein belonging to the neurotrophine family that promotes neuronal growth, differentiation and survival in different areas of central and peripheral nervous system. The molecular pathway that mediates the BDNF effects on cell survival is well known and documented [20]. Briefly, the homodimeric BDNF induces the dimerization of the thyrosin-kinase receptor B, the binding of ATP to the intracellular ATP-binding loop, and in turn the stimulation of the kinase activity. The autophosphorylation of the tyrosine triplet in the kinase domain is a prerequisite for further phosphorylation steps (via Src homology 2/collagen-related protein and PIK3and MAPK pathways) that finally mediate the effects of the neurotrophin on neuronal survival, differentiation, and gene expression as well as acute effects on synaptic transmission [21].

Also the molecular basis of GDNF mechanism of action is well know and consists essentially in its interaction with the GDNF-family receptor-alpha (GFRa1), on the activation of the Ret tyrosine-kynase [22] and on the PLCγ, PI3/Akt and MEK-ERK1/2 pathway [23]. Nevertheless, it is also known that the GDNF- GFRa1 complex can work independently from Ret activation by activating the Src family and consequently the c-AMP-response element binding protein (CREB) [24,25]. All these mechanisms have a central role in regulating the survival of dopaminergic neurons [26]. The precise balancing of these signals results in the definition of neuronal cell fate in response to different noxa.

In order to establish the role of the hypothesized mechanism of action, the ability to synthesize and secrete BDNF and GDNF by MSC from PSP patients and healthy donors has been evaluated, by real–time PCR and by ELISA. The results are shown in Figure 1 and they demonstrate that MSC from PSP are able to produce as main neurotrophine as MSC from healthy donors. For that reason, BDNF and GDNF secretion from MSC will be measured during the clinical protocol as potency assay. The use of cells instead of the simple administration of synthetic proteins has several advantages. First of all endogenously produced neurotrophines are in principle fully bio-available since MSC could be able to vehicle directly the neurotrophines to the damaged tissue. In this regard, it has been already demonstrated that MSC are able to overcome the brain–blood barrier [27,28]. MSC may also act by releasing extracellular vesicles, including exosomes and microvescicles, which transport lipids and different mRNA functional transcripts, microRNA, long non-coding RNA and occasionally genomic DNA and therefore they could be able to transfer genetic information that may induce transient or persistent changes in the recipient cells [29].

**Figure 1 F1:**
[figure not shown]
**Pre-clinical data.** Bone marrow mesenchymal stem cells from patients affected by progressive supranuclear palsy have the typical spindle-shaped morphology **(A)**, are positive for mesenchymal-specific antigens to an extended flow-cytometric analysis **(B)** and express BDNF and GDNF as those from healthy subjects, as demonstrated by real time PCR **(C)** and ELISA **(D)**. BM MSC: bone marrow mesenchymal stem cells; PSP: Progressive Supranuclear Palsy; HS: healthy subjects. The results of flow cytometric analysis, Elisa and PCR are expressed as mean (±SD).

## Methods/design

The current trial is a prospective, randomized, sham-controlled, phase I clinical study to evaluate the safety and efficacy of autologous mesenchymal stem cell intra-arterial infusion in patients with PSP. The protocol has been authorized by the local Ethics Committee of Fondazione IRCCS Ca’ Granda Ospedale Maggiore Policlinico of Milano, Italy, and by the National Competent Authority for phase I cell therapy protocol at Istituto Superiore di Sanità.

### Primary and secondary objectives

The primary objective is to assess the safety of autologous MSC therapy in patients with PSP in a “first-in-man” context.

The secondary objective is to assess the efficacy of autologous MSC therapy in patients with PSP in terms of stabilization or improvements in motor function, neuropsychological parameters and neuroimaging findings.

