### Statistics

#### General considerations

As noted above, the safety of cellular therapy administration in the first five patients will be reviewed by the Data Safety Monitoring Board. These reviews will be shared with our institutional IRB. If the treatment appears safe, as determined by the Data Safety Monitoring Board with institutional IRB agreement, the protocol may be reopened to treat a total of 20 patients.

For statistical analysis of efficacy endpoints, descriptive statistics are computed for variables of interest (mean and SD for continuous variables and frequencies for categorical variables). Test results are summarized over time using appropriate graphical or tabular formats. The non parametric pair wise Wilcoxon rank sum test will be used to investigate each variable within subject and between the same subject at different follow-up (e.g. pre- vs. post-MSC, pre- vs. post-sham, etc.). The use of a non-parametric test has been considered the most appropriate since the distribution of the variable is not known and the number of observations is relatively small. For each time point, the test will be performed with 20 paired values (the values before and after MSC therapy in the 10 subjects allocated to immediate treatment plus the 10 subjects allocated to the delayed treatment).

P-values < 0,05 will be considered statistically significant. Additional summary statistics are also considered as appropriate to the data.

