## Discussion

Cell-based advanced therapy is a novel and extremely promising option to cure otherwise untreatable neurodegenerative diseases but there are still several bottle necks that slow the progression and the widening of clinical trials in this context. Mainly, despite the overall positive results reported in several small studies in PD and MSA, there is a lot of uncertainness regarding the real capacity of MSC to reach the brain, the selectivity of their targets and their real mechanism of action. Moreover, in PD as well as in atypical parkinsonisms no validated biomarker is available to follow-up the neuroprotective effect of putative disease-modifyng treatments. So, why are we performing this trial? First: there are several positive results in other no-option parkinsonisms as well as in PD that deserve to be confirmed also in other pathologic context like PSP. Therefore, even thought the primary objective of this protocol is to demonstrate the safety of autologous MSC intra-arterial administration in subjects affected by PSP, we have designed a sham-controlled study, with the aim to document efficacy as well. Second, we would like to indirectly get information on the putative neuroprotective mechanism of action of MSC in PSP by comparing the in vitro results of the proposed potency assay and the clinical outcome. The biological hypothesis underlying the rationale of the proposed protocol is that MSC can reduce the neural cell loss in PSP by reducing cell apoptosis and the detrimental consequence of oxidative stress on neural cell homeostasis. Whit this premises, it should be clear to the reader that, the objective of making neurons from stem cells is out of the scope of our approach. Nevertheless, the story of replacing lost neurons in parkinsonisms by transplantation has been pursued for years. At first tissue was transplanted. In the 1980s autologous adrenal gland medullary tissue was transplanted first in animals and then in humans. Significant clinical improvements were achieved, but common and even serious postoperative complications induced clinicians to abandon this option [39-44]. In the 1990s non-autologous fetal neuron transplantation was attempted. Clinical benefits were modest and confined to younger patients (<60 years), and complications occurred i.e. the appearance of postoperative dyskinesias that in a few cases were severe and refractory to treatment. PET investigations suggested that these cases were due to an imbalance in the dopaminergic circuits induced by the transplanted cells [45,46]. Recent in vivo brain imaging findings in two patients, who had exhibited major motor recovery after transplantation, suggested that the cause of the dyskinesias was a serotonergic hyperinnervation [47]. An alternative explanation is that an immune response was responsible for both the appearance of dyskinesias and the modest extent of the therapeutic benefits [48]. Furthermore, the autopsies of subjects who had received fetal mesencephalic dopaminergic neurons disclosed the presence of Lewy bodies, raising the possibility of host-to-graft disease propagation. Thus, the prospects for dopaminergic fetal neuron transplantation in PD do not appear to be promising [49]. Autologous stem cell transplantation has been proposed for the most common form of parkinsonism, PD [50]. This proposal overcomes the ethical reservations related to the use of fetal cells or embryonic stem cells, and removes the risk of transplant rejection. Even thought the ability of different bone-marrow derived stem cells to migrate into the brain and to differentiate into cells bearing neural markers have been postulated even in vivo [51-53], the proven evidence of the so-called neural plasticity have never been demonstrated. Indeed, in the last years the attention of most investigators has been addressed to study the potential of BM mesenchymal stem cells to positively influence neural cell survival and to reduce cell apoptosis [54-56]. MSC have proved to be able to produce different kinds of growth factors that increase neuronal survival, to possess immunoregulatory properties able to influence inflammatory conditions and to migrate to damaged tissue areas where they might contribute to counteract neurodegeneration. What is more, they can be easily harvested from the bone marrow of the patients, easily expanded on a large scale for autotransplantation, and administered to patients via various routes [57]. MSCs have been isolated from PD patients and they do not differ from those of healthy subjects in terms of phenotype, morphology and ability to differentiate [58]. Furthermore, it has been demonstrated that MSCs exert neuroprotective effects on dopaminergic neurons both in vitro and in animal models of PD (rats given the toxin MG-132 or 6-OHDA), mediated by anti-inflammatory activity and the secretion of growth factors [59-62]. Of particular interest is the fact that in the rats given MG-132, a proteasome inhibitor, MSCs also reduced the accumulation of polyubiquinated proteins, a finding that suggests that they also contribute to correct proteasome dysfunction, which is believed to play an important role in the pathogenesis of PD [60].

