
Autologous MSC therapy would therefore appear to be an important candidate for the development of a parkinsonism-modifying therapeutic strategy.

To our knowledge, four pilot clinical trials have been published on the use of autologous stem cell transplantation in patients with primary parkinsonism. Two studies [63,64] have been conducted in patients with multiple system atrophy (MSA). The first one was an open-label, controlled trial designed to assess the feasibility and safety of MSC therapy by intra-arterial and intravenous route in which eleven MSA patients were infused MSC therapy through the internal carotid artery and the proximal portion of the vertebral artery once and by intravenous route thereafter once a month for three months. Treated patients were compared to 18 untreated control MSA patients. Follow-up was continued up to one year after the beginning of treatment and consisted in neurological examinations using the unified MSA rating scale scores (UMSARS). In addition, 5 treated patients and 10 untreated patients underwent brain metabolism imaging using PET and ^18^ F-fluoro-deoxyglucose (FDG). After 12 months mean total UMSARS score was similar to the score at baseline in the treated group (functional stabilization), whereas it had worsened in the control group (p = 0.002). Moreover, treated patients showed increased brain metabolism by means of FDG-PET, while the untreated group had decreased uptake. The most significant adverse events reported was the occurrence in 7 patients of small spotty lesions on MR images that were considered to be asymptomatic microemboli, a frequent complication of catheterization techniques. The same group recently published the results of a second protocol, in which thirty-three patients with probable MSA-C were randomly assigned to receive MSC via intra-arterial and intravenous routes or placebo. The primary outcome was change in the total UMSARS scores from baseline throughout a one-year follow-up period between groups. In this study, the MSC group had a smaller increase in total and part II UMSARS scores compared with the placebo group. Cerebral glucose metabolism and gray matter density were more extensively decreased in the cerebellum and the cerebral cortical areas, along with greater deterioration of frontal cognition in the placebo group compared with the MSC group. No serious adverse events directly related to MSC treatment were recorded. However, intra-arterial infusion resulted again in small ischemic lesions on MR. In another open-label clinical trial [65], autologous BM MSCs were transplanted into a sublateral ventricular zone of the brain by stereotaxic surgery in 7 male patients aged 22 to 62 years with advanced PD. The diagnosis was based on the presence of the classical symptoms and a good response to levodopa. The patients were followed up for 10 to 36 months. Three of the patients experienced motor improvement compared to baseline; the mean extent of improvement in UPDRS score was 22.9% in OFF and 38% in ON. Two of the patients were able to reduce the dosage of their antiparkinson medications. No serious adverse events occurred. MRI imaging did not disclose any significant changes. The last study [28] was an open-label clinical trial conducted by interventional radiologists, who subjected 53 patients with a diagnosis of PD made according to UK Brain Bank criteria to intraarterial autologous implantation of mononuclear cells from bone marrow. The cells were introduced by intraarterial catheterization, infusing the cells into the posterior part of the circle of Willis, from which the perforating arteries that irrigate the basal nucleus and the substantia nigra originate. Four patients received a second implant. None of the patients had major complications. They experienced major significant changes in median disease severity scores: UPDRS, Hoehn & Yahr, Schwab & England and Northwestern University Disability Scale (NUDS). In eight patients follow-up MR spectroscopy revealed mean improvements in n-acetylaspartate/creatine ratio. These studies demonstrated the feasibility of autologous cell transplantation in patients with parkinsonism, but they did not demonstrate efficacy, because their design did not ensure objective measurements. Also, clinical improvement could have been influenced by the beliefs of patients and investigators alike as they were open-label studies. Neuroimaging changes could not be easily dismissed, but they were available only in a few patients and did not focus on the kind of damage that is seen in parkinsonism. A search in the WHO worldwide clinical trial database on August 1, 2013 disclosed 390 studies assessing MSC therapy. Out of these only other three studies are ongoing in patients with Parkinson. To our knowledge this is the first time that autologous MSC therapy is given to PSP patients.

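### Slowed decline relative to sham is neither named in the efficacy objective nor estimated by any stated efficacy test, although it is the effect the trial's rationale points to

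*Protocol article*

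**What the plan says.** All references are to the protocol article.

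- **Primary and secondary objectives.** Safety is primary. Efficacy is secondary and is to be assessed "in terms of stabilization or improvements in motor function, neuropsychological parameters and neuroimaging findings".
- **Abstract, Discussion.** The trial is meant to test safety and to "exploit the properties of autologous mesenchymal stem cells in reducing disease progression".
- **Discussion, biological hypothesis.** The premise is that "MSC can reduce the neural cell loss in PSP by reducing cell apoptosis". Replacing neurons is expressly not the goal.
- **Discussion, earlier trials.** In the randomised MSA trial, "the MSC group had a smaller increase in total and part II UMSARS scores compared with the placebo group". In the open-label controlled MSA trial, the mean 12-month score was "similar to the score at baseline in the treated group (functional stabilization"; the untreated controls worsened.
- **Statistics, General considerations.** A paired non-parametric test is applied to each variable within patients ("e.g. pre- vs. post-MSC, pre- vs. post-sham, etc"). "For each time point, the test will be performed with 20 paired values": ten patients from each treatment sequence. "P-values < 0,05 will be considered statistically significant"; sidedness is not given.
- **Motor function; Neuropsychological assessments.** Changes in score are described. No responder cut-off is set.
- **Multifactorial movement analysis.** A before/after signed rank test is planned, plus a Mann–Whitney comparison of patients with healthy volunteers.
- **Neuroimaging assessment.** An ANOVA is planned. Its factors are not stated.
- **Study design.** Patients are randomised to immediate MSC or immediate sham and switch after 6 months.

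**The concern.** The objective and the general efficacy test share one reference point, the patient's own baseline. A treatment that reduces cell loss predicts a slower decline, and stabilisation only if the loss stops altogether. PSP is progressive: the Background gives a wheelchair after 5 years on average and a mean survival of 7 years. Patients are therefore expected to get worse over the study even if MSC helps.

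Under those conditions a before/after comparison mixes the natural course with the treatment effect. A real slowing can look like deterioration after MSC. A useless treatment in slowly declining patients, tested in a small sample, can look like stabilisation. The trial randomises to sham and blinds its assessors, so it has the contrast that would separate these cases, but no stated efficacy analysis uses it. What is at stake is the interpretation of the exploratory efficacy data.

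**Working it through.** **The plan's own figure.** 10 + 10 = 20 pairs, as stated. This is a count; the article gives no effect size or power.

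**Inputs.**

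- From the article: 20 pairs, 10 patients per arm, level 0.05.
- Assumed: two-sided tests; normally distributed changes with SD 1; untreated mean worsening *d* = 0.5, 1.0 or 1.5 SD of the change score; slowing *s* = 0, 30, 50 or 70%; the same *d* and SD in all patients and over each test interval.
- General considerations calls the test a pairwise rank sum test. Because the values are paired, the signed rank test was used, as named in Multifactorial movement analysis.

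**Method.** Mean change after MSC = *d* × (1 − *s*). For each setting 4,000 trials were simulated with two tests: a signed rank test on 20 before/after pairs, and a Mann–Whitney test of change in 10 MSC versus 10 sham patients.

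| *d* (SD) | *s* | Mean change after MSC | Before/after: worse, p<0.05 | Before/after: not significant | Before/after: better, p<0.05 | 10 v 10: favours MSC, p<0.05 |
|---|---|---|---|---|---|---|
| 0.5 | 0% | 0.50 | 53.7% | 46.3% | 0.0% | 2.1% |
| 0.5 | 30% | 0.35 | 29.5% | 70.5% | 0.0% | 4.3% |
| 0.5 | 50% | 0.25 | 18.2% | 81.7% | 0.2% | 6.8% |
| 0.5 | 70% | 0.15 | 9.0% | 90.6% | 0.4% | 9.1% |
| 1.0 | 0% | 1.00 | 99.0% | 1.0% | 0.0% | 2.2% |
| 1.0 | 30% | 0.70 | 82.8% | 17.2% | 0.0% | 8.9% |
| 1.0 | 50% | 0.50 | 55.0% | 45.0% | 0.0% | 17.0% |
| 1.0 | 70% | 0.30 | 24.3% | 75.6% | 0.1% | 28.0% |
| 1.5 | 0% | 1.50 | 100.0% | 0.0% | 0.0% | 2.3% |
| 1.5 | 30% | 1.05 | 99.2% | 0.8% | 0.0% | 13.7% |
| 1.5 | 50% | 0.75 | 88.1% | 11.8% | 0.0% | 30.3% |
| 1.5 | 70% | 0.45 | 45.1% | 54.9% | 0.0% | 55.2% |

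**Reading the table.**

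1. A slowing of 30 to 70% almost never appears as significant improvement (at most 0.4%). It appears as worsening or as a non-significant change.
2. Compare *d* = 0.5 with no effect and *d* = 1.0 with the decline halved. Both give a mean change of 0.50 SD, and the before/after test behaves alike in both (53.7% and 55.0% worse; the gap is simulation error). That test cannot tell an ineffective treatment in slow decliners from a halving of decline in faster decliners.
3. The between-arm test targets *d* × *s*, which is the slowing itself. With no effect it favours MSC in about 2% of trials, close to the nominal 2.5% in that direction.

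**Hand check of the between-arm figure.** Standard error of the difference = √(1/10 + 1/10) = 0.447 SD. For *d* = 1.0 and *s* = 50% the difference is 0.5 SD, and 0.5/0.447 − 1.96 = −0.84, which gives a power of about 20%. The simulated rank test gives 17%. The 95% interval extends about 1.96 × 0.447 = 0.88 SD either side of the estimate.

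**The case against.** The strongest reply is that the objective is one general sentence for a secondary aim of a first-in-man safety study, and that the article itself calls its look at efficacy preliminary. Nothing turns that sentence into a decision rule. Stabilisation also has a basis in the cited evidence: the open-label MSA trial reported it, and reduced cell loss does not exclude it. Changes under sham are to be analysed as well as changes under MSC, so a smaller decline after MSC could be seen and described. The percentages measure the uncontrolled before/after test rather than the wording of the objective, and they depend on decline rates that the article does not supply.

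Most of this stands and limits the point. A reader might infer that a slowed decline would count as failure and be reported as no efficacy, or that it would drive a wrong efficacy go/no-go. The article does not support that. It contains no success criterion, no responder definition and no efficacy gate; its only gate is the safety review after the first five patients. At low decline rates the error can also run the other way, towards calling a change stabilisation.

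Two things remain. The article says that the earlier studies did not demonstrate efficacy, so the open-label stabilisation is a weak reason to leave slowing out. And separate before/after tests for MSC and for sham do not estimate the difference between them, however both are described.

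**Conclusion.** The point holds in limited form. The objective names stabilisation or improvement. The stated aim, the hypothesis and the cited randomised MSA result point to slowed decline. No stated efficacy test estimates the MSC-versus-sham difference in change; the imaging ANOVA might, but its factors are not given.

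If the decline is truly halved, the 20-pair test shows significant worsening after MSC in about 18%, 55% and 88% of trials for an untreated decline of 0.5, 1.0 and 1.5 SD of change. With no effect and 0.5 SD, about 46% of trials are non-significant. These figures assume normal changes, a common decline rate and two-sided tests. The range is wide because the article gives neither the decline nor its SD. That the before/after test confounds natural course with treatment effect does not depend on them. The primary safety objective is unaffected.

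**What to change.** 1. Extend the secondary objective so that efficacy includes less worsening than under sham over the 6-month sham-controlled period, with full stabilisation and improvement as stronger grades of the same effect.
2. Make the main efficacy analysis the MSC-minus-sham difference in change from baseline to 6 months between the randomised arms, with a confidence interval. A rank-based version (Mann–Whitney test with a Hodges–Lehmann interval) keeps the plan's non-parametric preference.
3. Keep the pooled before/after tests as descriptive summaries.

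The cost is wording and one analysis, with no new patients. The planned before/after-sham comparison and the pre-MSC value in the delayed arm already imply an assessment at about 6 months; the visit schedule should confirm that both arms have one before the switch.

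The downside is precision. Ten versus ten gives about 17% power at a 1.0 SD decline with 50% slowing, and about 4% to 55% across 0.5 to 1.5 SD and 30 to 70% slowing. The result should be presented as an exploratory estimate, and a non-significant difference should not be read as absence of effect.
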